**Fig. 1 Fig1:**
[figure not shown]
Recruitment and procedure of the study

### Interventions

#### Lifestyle intervention

The lifestyle intervention combines psycho-education on a healthy lifestyle with a lifestyle program focusing on improving physical exercise, healthy eating behaviors, sleeping patterns, and screen time. Based on previous research, an integrated approach (including psycho-education and skills training) has the best chance of being successful [19–21]. At the start of the intervention, children and their parents will set the goals they want to obtain at the end of the intervention (i.e., after 12 weeks). This is a tailored-based intervention, meaning that the goals and the resulting focus of the content of the intervention can differ for each family. However, the same techniques, structure, and working elements are used equally (see Table 1).

**Table 1 Tab1:** Sessions of the lifestyle treatment at location

Session	Topic	Goal
1	Introduction to treatment	• In this session, treatment goals are established. To achieve these goals, both the child and the parent(s) must support them. Together with the practitioner, it is discussed which goals are set up for achievement in the next 12 weeks
2	Psycho-education on healthy eating behavior and exercise	• This session explains more about healthy eating behavior and physical activity
		• For healthy eating behavior, the psycho-education is based on the most recent Dutch dietary guideline and the recommended daily consumption of food groups per sex and age group developed by The Netherlands Nutrition Center (Voedingscentrum). For physical activity, parents and children will be educated using ‘the Beweegrichtlijn 2017 for children^a^
		• During the session, it is discussed how parents and children’s eating habits and exercise levels can be embedded in their lives
		• At the end of the session, the completed food diary of the child is discussed to get a better insight into their eating patterns
3	Psych-education on healthy sleeping habits and screen time use	• This session explains more about healthy sleeping habits and screen time use
		• During this session, it is discussed how the sleeping habits and amount of screen time used by parents and the child are embedded in their lives
		• At the end of the session, the completed sleeping diary of the child is discussed to get a better insight into their sleeping pattern
4	PMST: Interaction patterns and qualities	• This first PMST session aims to get a deeper insight into the different patterns in the family. Moreover, multiple assignments are done together with the whole family to get a better understanding of everyone’s role in the family. This allows interaction patterns between family members to be better investigated and understood
5	CBT: Learning about thinking	• This session aims to give a better understanding of the coherence between thoughts and behavior based on the CBT perspective. Hereby, lifestyle behavior is linked to possible underlying thoughts
6	CBT: Emotions and signaling plan	• This session aims to get a better insight into the different emotions people have. In this session, these different emotions are linked to lifestyle behaviors (e.g. happiness and cycling, or loneliness and gaming)
7	PMST: Emotions and signaling plan	• This PMST session aims to transfer what was learned from session 5 into body-oriented exercises in the gym
8	CBT: Helping thoughts. PMST: feedback on video’s from PMST together with parents	• This session aims to understand ‘helping thoughts’. Thoughts can help when children are worried about things. These helping thoughts are linked to situations when it is difficult to maintain a healthy lifestyle behavior and the obtained goals
		• In the same week, parents look back at the video recordings from PMST sessions. The therapist provides feedback on these sessions with the aim of gaining a better understanding of the interactions in the family
9	PMST: Experimenting with new behavior	• This PMST session aims to practice new behavior linked to the goals. Together with the PMT therapist assignments on goal-setting are done body-oriented
10	PMST: Positive attention and ‘breaking the negative interaction spiral’	• This PMST session aims to get a better insight into the interaction patterns in the family. The focus lies on increasing positive attention and breaking the negative interaction spiral
11	Relapse prevention	• In this session, the learned behavior will be retained. Furthermore, a joint plan is made with steps to take when maintaining the new behavior becomes difficult again (i.e., a relapse prevention plan)
12	Evaluation and closing	• This last session evaluates the therapy session and the goals

Parallel to these sessions on location, the family will receive visits from the homecoach. The order of the sessions is the guideline for the intervention, however, a certain degree of flexibility is required and accepted in order to make the intervention fit to the family

*CBT* Cognitive Behavioral Therapy, *PMST* Psychomotor Systematic Therapy

^a^The Beweegrichtlijn 2017 advises children (4–18 years) to exercise moderately for at least an hour a day. Longer, more frequent, and/or more intensive exercise provides additional health benefits. Furthermore, children are advised to do muscle and bone-strengthening activities at least three times per week and to avoid a sedentary lifestyle

This intervention will be given by trained mental health professionals (i.e., psychologists and nursing specialists). Prior to the start of the intervention, these professionals received a three-day training by experts in the field focusing on sleep-promoting behavior, healthy eating behavior, screen time (addiction), and motivational interviewing.

The lifestyle intervention consists of a 12-week program (see Table 1) where the child and parents are treated intensively (approximately two hours a week). The intervention will start with psychoeducation sessions on a healthy lifestyle. In addition to providing more information about a healthy lifestyle, psychological treatment is necessary to achieve and maintain behavioral change. CBT has great evidence as an effective intervention method for behavioral change in mental health problems in adults and children (e.g., sleeping problems and eating disorders) [22]. Due to the amount of evidence of CBT, and the focus on both cognitions and behavior in lifestyle behavior, this psychological treatment was chosen for this intervention. A workbook is available for the child and the parents and contains information about a healthy lifestyle and describes the various assignments in detail. See Table 1 for a more detailed description of the content of the sessions. While the order of the sessions is the guideline of the intervention, a certain degree of flexibility is needed to fit the family's needs.

These CBT sessions will be combined with PMST sessions for children and their parents. Because of this combination, children and parents can use the behavioral skills they have learned during CBT (e.g., behavioral experiments; using helpful thoughts) in assignments of the PMST. In this way, parents and children will get concrete examples of applying the learned CBT techniques. In PMST, children and their caregivers both learn skills (i.e., action-oriented approach) but also experience and get more knowledge about emotion regulation and how it feels in your body (i.e., experience-oriented approach) [16]. Furthermore, systemic interaction patterns between family members are quickly established. The PMST sessions will be held in the gymnasium.

In addition to the CBT and PMST sessions on location, there will be weekly visits by a home coach since family support at home is crucial for the child. The home coach will visit families in their homes each week to promote healthy behavior and help families apply new lifestyle skills. This home coach may also visit schools and sports clubs with the child to involve (and, if necessary, educate) teachers and trainers. The coach plays a crucial role in creating a healthy eating, exercise, and sleep environment in the family as well as setting boundaries and focusing on self-empowering the system. Targeting a child’s whole system and social context will promote lasting behavioral changes and family satisfaction. The home coach will discuss personal goals continuously with the children and their caregivers. The step from ‘no change’ to ‘some change’ is the most crucial. Targeting the family will stimulate the child and promote lasting behavioral changes.

The main focus of the treatment, regarding the different lifestyle items, is described below.A.SleepFor sleep problems, the focus will be: education on sleep hygiene, addressing a shift in the biological clock, and CBT. This entails 1) psycho-education regarding normal sleep and good sleep habits; 2) choosing optimal and regular bedtimes, bedtime fading, and sleep restriction; 3) optimizing sleep hygiene, especially concerning the use of screen time before bedtime and incorporating a good ritual before bedtime; 4) optimizing the amount and timing of physical activity and light exposure; and 5) optimizing stimulant medication (optional) for the child regarding sleep problems.B.Screen time useEducation on a healthy lifestyle and CBT will be applied to screen time use. This entails 1) psycho-education regarding everyday screen time use, 2) choosing optimal screen use time, and 3) supporting other activities that do not include screen time.C.Healthy eating behaviorsFor healthy eating behavior, education on a healthy lifestyle and CBT will be applied. With this, the focus will be on improving nutritional food intake. Parents and children will be educated on the most recent dietary guidelines by The Netherlands Nutrition Center, part of The European Public Health Nutrition Alliance (EPHNA) and the recommended daily consumption of food groups per sex and age group. Moreover, with parents and children, ways to make healthy food intake more accessible are investigated.D.Physical activityEducation on a healthy lifestyle and CBT will be applied to physical activity. The focus will lay on the improvement of the amount of physical activity. As part of the lifestyle intervention, the child will practice in the gym with a mental health professional and together with the family during PMST. Parents and children will be educated on ‘The Dutch Beweegrichtlijn 2017 for children’ which is comparable for children with the World Health Organization [23] guidelines on physical activity and sedentary behaviour to create more awareness and knowledge on the recommended amount of physical activity per week. Moreover, the therapy will focus on ways to promote physical activity and make it easier for them in daily practice.

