### Quantitative study

#### Participants

The medical ethics Committee on Research involving Human Subjects of Radboudumc (CCMO, Arnhem-Nijmegen) approved the study and it is registered under 2021–8224. Written informed consent regarding participation and publication from all parents or guardians for participants under 16 years will be obtained during the randomized controlled trial.

Participants will be recruited among new referrals at Karakter Child- and Adolescent Psychiatry and Denkkracht, The Netherlands. Karakter is a hospital for specialist mental health care, and Denkkracht a center for neuropsychological expertise. The selection of participants is a 2-step process. First, our digital intake questionnaire is used to select potential participants. Before the first appointment at the clinic, parents must complete this digital intake questionnaire. This assessment includes age, sex, country of birth, and parents’ educational level. In the section on lifestyle, various questions about physical exercise, healthy eating behavior, sleeping patterns, and screen time are asked. Potential participants are selected when they positively respond to one or more of the following questions:How much time does your child spend in front of a screen compared to peers (*More* or *Much more*)How much exercise does your child have compared to peers? (*Less* or *Much less*)How often does it take longer than 30 min for your child to fall asleep? (*Always*)How often does your child wake up more than three times per night, or does your child lie awake for more than 20 min per night? (*Always*)How often does your child wake up before 6 am? (*Always*)How often does your child experience daytime fatigue? (*Always*)How many days a week does your child eat breakfast? (*(Almost) never* or *1–2 days a week*)How many days a week does your child eat fruit? (*(Almost) never* or *1–2 days a week*)How many days a week does your child eat vegetables? (*(Almost) never* or *1–2 days a week*)How many times a day does your child get snacks (biscuits, candy, chips)? (*5–6 times a day* or *More than seven times a day*)How many days a week does your child eat “fast food” (pizza, chips, pancakes, chip shop, snack bar, etc.)? (*5–6 days a week* or *Every day*)

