Secondly, following a positive response to these items, participants are invited for a somatic assessment and eligibility check for the Movementss study by a nurse specialist and child and adolescent psychiatrist. Somatic assessment includes measurement of weight, height, blood pressure, heart rate, head circumstances, an inspection of dysmorphic features, and motor functioning and coordination.

For eligibility, participants must meet the following criteria: 1) 6–12 years old at the inclusion date, 2) DSM-5 diagnosis (any presentation), 3) somatic or lifestyle problems assessed by somatic examination and lifestyle screening (overweight, obesity, underweight, unhealthy diet, sleeping problems, inactivity, and screen time use), and 4) willingness to set lifestyle goals. Comorbidities are allowed except for eating disorders (i.e., anorexia or bulimia nervosa) and diabetes mellitus. Exclusion criteria are: 1) unable to respond to questions (parents or children), 2) no access to a home internet connection, 3) insufficient mastery of the Dutch language in parents or children, 4) physically incapable of doing physical exercises, 5) surgery in the past six months or next twelve months impacting physical activity or dietary intake, 6) any somatic condition severely restricting diet, current treatment for the psychiatric diagnosis, and 7) an intelligence quotient (IQ) below 70. Participants receiving this lifestyle intervention cannot start any other treatment during the 12-week-long lifestyle intervention, except for the optimization of pharmacotherapy. For children who receive medication, this will be optimized during the lifestyle intervention. During this optimization, the physical health of the children will be closely monitored since lifestyle-related problems (e.g. sleeping problems, reduced appetite, and overweight) more often occur when using medication. Similarly, participants receiving CAU will receive one session of digital psycho-education on a healthy lifestyle though they will not follow a lifestyle intervention.

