#### Randomization

The Movementss study is a two-arm randomized controlled trial; patients fulfilling eligibility criteria and willing to participate will be randomized after baseline assessment (1:1 allocation ratio) in either the lifestyle intervention or CAU group using block randomization, with varying random block sizes of 2, 4 or 6. A priori, an independent statistician will prepare a computer-generated randomization schedule stratified for weight (underweight, normal, overweight), sex (male, female), and age (6–8 years, 9–12 years) to ensure that the number of participants in both treatment arms is closely balanced within each stratum. Castor EDC will be used for the actual randomization process. After obtaining informed consent and baseline measurements, the study coordinator will provide the randomization code. Participants, researchers, and practitioners are aware of treatment allocations.

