### Sample size and power

A sample size calculation using G-power 3.1 was conducted for the primary outcome measure, defined as the mean difference in the quality of life between two groups at three time points (baseline, 12 weeks intervention, 26 weeks follow-up). We used historical data on the Kidscreen-27 (a measure of QoL) from our own population to estimate the effect size. To detect a median effect size (Cohen’s f = 0.39) with a two-sided significance level of 5% and power of 80% with equal allocation to two arms would require 66 patients in the trial. To allow for 20% drop-out, 80 children are recruited in total.

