#### Secondary study parameter(s)

Concerning secondary outcome measurements, repeated measures techniques based on the intention-to-treat principle will be used to analyze the difference between the lifestyle intervention and the CAU group.

To get more insight into the prior beliefs of parents about short-term and long-term success, the outcomes of the 5-item questionnaire will be analyzed using the independent samples *t*-test to compare the lifestyle intervention group with the CAU group. Patient satisfaction and compliance with the intervention will be measured using the satisfaction measurement scale. The outcomes will be evaluated with a repeated-measures design.

The cost-effectiveness of the lifestyle intervention is measured with the TiC-P questionnaire. To assess this outcome, we will use an independent sample *t*-test to compare the lifestyle intervention with the CAU.

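### A single arm difference in BMI cannot be read as benefit or harm, because underweight and overweight children are both enrolled and improvement runs in opposite directions

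*Protocol article*

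**What the plan says.** - **Entry.** The somatic or lifestyle problems that qualify a child (Participants) are "overweight, obesity, underweight, unhealthy diet, sleeping problems, inactivity, and screen time use". Weight problems in both directions therefore count.
- **Randomisation.** The schedule is "stratified for weight (underweight, normal, overweight", as well as by sex and age group (Randomization). The plan thus expects children in all three weight classes.
- **Tailoring.** Under Lifestyle intervention, "the goals and the resulting focus of the content of the intervention can differ for each family".
- **Outcome.** The Abstract lists BMI among the physical measurements that are secondary outcomes. The second aim, at the end of the Background, names weight status. Under Somatic measurements, height and weight are repeated at T1 and T3, and overweight and obesity prevalence are defined by age-referenced cut-offs. No corresponding outcome is defined for underweight.
- **Analysis.** For secondary outcomes, "repeated measures techniques based on the intention-to-treat principle will be used to analyze the difference between the lifestyle intervention and the CAU group" (Secondary study parameter(s)). No term or subgroup for weight class is mentioned. The adjustment factors named under the primary outcome are age group and sex.
- **Effect modification.** The Background plans to look for moderators of adherence or response and gives socio-economic status, ethnicity and comorbidity as examples.

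**The concern.** A difference in means is informative when a higher value is better for everyone, or worse for everyone. Mean BMI in this sample does not meet that condition. In the overweight stratum success lowers it, in the underweight stratum success raises it, and in the normal stratum success is staying put. The pooled contrast adds these with opposite signs, so its size and sign depend on the weight mix recruited as well as on what the intervention did.

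What is at stake is the weight-status part of the second aim. A programme that helps both weight groups could be reported as having no BMI effect. A small fall in mean BMI could be reported as success when it came from underweight children losing weight. Allocation is known to participants, researchers and practitioners, so a breakdown by weight class chosen after the results are seen would look data-driven.

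**Working it through.** **Inputs from the article.** Analysed number 66, so 33 per arm; two-sided 5% level; 1:1 allocation (Sample size and power). That section concerns KIDSCREEN-27 and gives "f = 0.39) with a two-sided significance level of 5% and power of 80"%. The figure of 66 is matched within two patients by a 2-df F test with non-centrality f² × N, which needs 67 and gives power 0.797 at 66. It is used here only as the number analysed. No BMI effect size is given.

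**Assumptions, not in the documents.** Shares p_over and p_under of overweight (including obese) and underweight children; a move of 0.3 SD of standardised BMI towards the healthy range in each of these groups; no change in normal-weight children.

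**Step 1: pooled difference (intervention minus CAU).**

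Pooled = -0.3 × p_over + 0.3 × p_under. Average movement towards the healthy range = 0.3 × (p_over + p_under).

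| p_over | p_under | Pooled difference (SD) | Average movement (SD) |
|---|---|---|---|
| 40% | 0% | -0.12 | 0.12 |
| 40% | 10% | -0.12 + 0.03 = -0.09 | 0.15 |
| 40% | 20% | -0.12 + 0.06 = -0.06 | 0.18 |
| 30% | 30% | -0.09 + 0.09 = 0 | 0.18 |

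The offset is partial in general. It is complete only when share times effect is equal on both sides.

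**Step 2: the same pooled value from opposite findings.** Take 40% overweight and 20% underweight.

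- Both groups improve by 0.3 SD: -0.3 × 0.4 + 0.3 × 0.2 = -0.06.
- Overweight children do not change and underweight children lose 0.3 SD: 0 × 0.4 - 0.3 × 0.2 = -0.06.

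The first is benefit in both groups and the second is harm in one, and the pooled mean cannot separate them. This ambiguity does not depend on the value 0.3 or on the exact shares; it needs only that both groups are present.

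**Step 3: do the other stated outcomes close the gap?** Overweight and obesity prevalence has a clear direction. However, an underweight child who reaches normal weight is not overweight before or after, so recovery from underweight leaves that prevalence unchanged. Adding weight stratum as a covariate would not help either: it shifts the stratum means but still fits one common arm effect.

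**Step 4: what stratum estimates can deliver.** With 66 analysed, 40% is about 26 children (13 per arm) and 20% is about 13 (6 to 7 per arm). Two-sample t-test, two-sided 5%, 0.3 SD:

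- overweight, 13 per arm: power 0.114;
- underweight, 7 per arm: power 0.081 (0.076 at 6 per arm).

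The approximate 95% half-width is t × √(2/n) in SD units: 2.064 × √(2/13) = 0.81 for the overweight stratum and 2.179 × √(2/7) = 1.16 for the underweight stratum. These estimates describe direction; they do not test it with any force.

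**The case against.** The other side has several good points.

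- **Analysis-plan detail.** The article gives one general sentence for all secondary outcomes. The BMI scale, interactions and subgroups are often left to an analysis plan, which is not shown. That is fair, and silence on those details is not the complaint. The complaint is that the contrast which is stated does not suit mean BMI in a population the article itself divides by weight class.
- **Prevalence and moderators.** Overweight and obesity prevalence is directional, and the moderator list is open. Both are true, but prevalence misses underweight and the list does not commit to weight class.
- **Validity of the pooled estimate.** The randomised all-children difference is unbiased for the average effect. This stands, and it is a reason to keep reporting it.
- **Weak remedy.** Stratum estimates will be imprecise. This also stands.

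A reader might infer more than the documents support. That BMI effects cancel outright is not shown: no weight mix or BMI effect is given, and exact cancellation is a special case. A reader might also argue that sleep, diet, activity and screen-time effects are lost by dilution, because "Potential participants are selected when they positively respond to one or more of the following questions" and a child without a problem in a domain cannot improve on it. The article does not bear that out. Sessions 2 and 3 cover all four domains for every intervention child, and several screening cut-offs are extreme (the sleep items count only at the always response), so a child who screens negative may still have room to improve. The all-children estimate for each domain is a legitimate target, and restricting it to screen-positive children is a trade-off.

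**Conclusion.** The point holds for BMI and weight status as secondary outcomes. Given the eligibility rule and the weight strata, one pooled difference in mean BMI has no single direction of benefit, and a null or signed result could not be interpreted alone. That conclusion rests on the text and needs only that both underweight and overweight children are recruited. The size of the offset rests on assumptions: with a 0.3 SD move in each group and 40% overweight, the pooled difference goes from -0.12 SD with no underweight children to -0.06 SD with 20% underweight.

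The loss is in interpretation and power; the randomised comparison is not biased. KIDSCREEN-27, the primary outcome, has one direction of benefit and is untouched. The point is worth settling before the data are seen, but it does not threaten the trial's main conclusion.

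**What to change.** State in the analysis plan, before results are known, that BMI will be standardised for age and sex and analysed in one of two ways:

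1. as distance from the healthy range, using the same weight-class limits that define the randomisation strata, so that a smaller value is better for every child; or
2. with an arm-by-weight-stratum interaction that uses the randomisation strata.

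In either case, report the arm difference within each weight stratum with a 95% confidence interval, labelled descriptive. Keep the all-children mean difference in the report, with a sentence saying that it is not to be interpreted alone.

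Analyses of each lifestyle domain among children who screened positive for it at intake are optional. If done, they should be labelled exploratory and shown beside the all-children estimate. Intake answers and weight stratum are fixed before randomisation in both arms, so grouping by them is valid; grouping by family goals would not be, because those are set at the start of the intervention.

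The cost is analysis wording only, as the data are already collected. The downside is small strata, wide intervals and more estimates on the page, which is why they should be descriptive. A distance score will also be zero for many normal-weight children and therefore skewed, so the model or interval method should allow for that.
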